#### Data Collection

Following best practice, a topic guide for the interviews will be used with questions and prompts for cognitive interviewing that follow guidance defined by ISPOR [40] (Multimedia Appendix 2). Prior to the interview, informed consent and selected background (clinical and sociodemographic) characteristics of the participants (including gender, age, ethnicity, employment status, income level, educational level, marital status, questions on disease severity, and questions on treatment) will be collected using an online survey. Interviews will be recorded and transcribed using intelligent verbatim transcription (being anonymized in the process). While ideally iterative, one round of cognitive interviewing is proposed in this study given available resources and recruitment challenges in ultra-rare diseases [32]. Instead, refinements made during cognitive interviewing are triangulated with patient and clinical input (PAG and MAG) to ensure lived experience input into decision-making. A similar approach has been adopted in the development of other rare disease PROMs [36,41].

The interviews are scheduled to last up to 1 hour, and the setting for the interviews is online. This choice of setting is both pragmatic, helping to enable efficiency in a rare disease [20], and methodologically sound. Research supports the use of online interviewing and the digital administration of PROMs as broadly equivalent to face-to-face or paper-based methods [42,43]. Participants receive an Amazon e-voucher of equivalent value in their own currency for taking part in the study.

#### Analysis

The transcribed qualitative data will be analyzed against an existing framework of themes for collating evidence on content validity in NVivo using framework analysis [44], a common approach to analyzing qualitative cognitive debriefing data [45,46]. Framework analysis is a systematic yet flexible approach unaligned with any specific epistemological, philosophical, or theoretical stance [47]. Reflexivity will be addressed by recognizing and transparently reporting the potential influence of researchers’ characteristics and a priori expectations on analytic decisions, alongside the use of team-based coding discussions to critically examine and moderate bias. The trustworthiness of the analysis will be addressed in several ways. Credibility will be enhanced through peer debriefing with patient representatives and researcher triangulation. Dependability will be strengthened through dual coding of the transcripts. Confirmability will be supported by an audit trail documenting analytic decisions and grounding findings in the qualitative data. Transferability will be enhanced through thick description of the research context, data, and findings [48].

Evidence from the framework analysis will be summarized qualitatively, and recommended revisions to the draft PROM will be tabulated for discussion with the PAG (session 1) and MAG (session 2). This may include revisions to items and PROM content, as well as the addition and removal of items. Any revisions and the rationale for them will be systematically tracked in an item-tracking matrix to provide rigor in the evidence base supporting PROM development [17,40]. Throughout item refinement and PROM design, the perceived respondent burden of ISBUS will be assessed through discussions with advisors in the PAG and MAG.

### Stage 3: Final Item Selection

#### Overview

Stage 3 of the project involves an online quantitative survey, in which the refined draft PROM (from stage 2) is administered alongside additional sociodemographic questions, clinical questions, and validated measures of symptom severity or HRQoL. The objective of this stage is twofold. First, to assess how the draft PROM performs statistically, with a view to making informed item selection decisions to reduce the content in the final PROM and maximize parsimony. Second, to provide preliminary psychometric evidence on the reliability and validity of the final PROM, including structural validity, hypothesis testing for construct validity, and internal consistency.

#### Participants and Recruitment

Participants for stage 3 are recruited via the same 2 pathways as described in stage 2 (ie, CDCN and clinician flyer with survey link), using convenience sampling to recruit as many eligible participants living with iMCD as possible. An ideal target sample size is ≥100, as simulations have suggested that samples of 100 and above produce more stable estimates in advanced psychometric analyses used in PROM development, such as Rasch model analysis [49]. To maximize the pool of potential recruits, patients who participated in stage 2 will be invited to participate in stage 3. Nevertheless, a sample of 100 may not be achievable given the rarity of the condition. Instead, an absolute minimum target sample size of 50 is adopted, as there is some evidence that this is a reasonable absolute minimum for conducting exploratory factor analysis [50]. Psychometric analyses will be adapted, as appropriate, to the final sample size (details provided in the Analysis subsection). Recruitment will continue until the minimum target sample is achieved.

As part of additional exploratory work for one of the project collaborators, English-speaking patients will be recruited from a health care site in Brazil. They are required to self-declare at least a B2 English language level [51]. These participants will be included in exploratory analyses only and not as part of the PROM development described in this protocol.

#### Data Collection

Survey content (Multimedia Appendix 1) will be agreed on alongside the PAG and clinical advisors prior to launch. The setting for the survey will be online to maximize recruitment numbers in a rare disease. Research suggests that electronic and paper-based PROM administration is broadly equivalent [43], and changing the mode of administration represents a minor to moderate modification that is unlikely to have a significant impact on scores [52]. However, it should be transparently acknowledged that mode of administration can affect who completes the survey (ie, the sample characteristics) [53,54].

After following a link to the online survey, participants provide informed consent and complete the iMCD screener described in stage 2. Those who pass the screener are considered eligible and proceed to answer sociodemographic and clinical background questions (ie, age, gender, country of residence, employment status, educational level, ethnicity, relationship status, age at the time of iMCD diagnosis, and iMCD treatment). Participants are then asked a single question on the impact of their iMCD symptoms on their daily activities (split into 3 options: no symptoms, symptoms but no impact on daily activities, and symptoms that are impacting daily activities).

Following these background questions, participants complete a draft version of the ISBUS PROM. Participants are then asked to rate the perceived importance of including each draft PROM symptom item in the final questionnaire on a 4-point Likert scale (0=not at all important; 3=very important). Participants then complete a 100-point visual analog scale with the stem, “Thinking about iMCD, how would you rate your quality of life during the past seven days?” (0=worst imaginable quality of life; 100=best imaginable quality of life). Next, participants are asked to complete the Patient Health Questionnaire-15 (PHQ-15), which measures physical symptoms [55], and the EQ-5D-5L (which measures health status [56]) for their country (US English was used for Brazil). Finally, participants are asked to leave their email address for reimbursement and to be contacted about participation in stage 4. Participants receive an Amazon e-voucher for taking part in the study (in their respective currency).

The 2 comparator measures were selected a priori based on their conceptual relevance and established psychometric performance. The PHQ-15 is a measure of somatic symptom severity that assesses the burden of common physical symptoms and has been widely validated across clinical populations. The EQ-5D-5L was selected to assess the relationship between symptom burden and broader HRQoL. We expect to observe at least moderate positive correlations between ISBUS and the PHQ-15 and moderate negative correlations between ISBUS and the EQ-5D-5L (ie, *r*_s_≥0.30). Only 2 additional PROMs were included to manage participant burden, given the length of the draft ISBUS PROM administered and the additional questions included.

#### Analysis

Table 2 outlines the planned psychometric analyses to be conducted as part of the ISBUS project. Analyses will be adapted to the actual sample size achieved (ie, ≥50 or ≥100) and will include, at the very least, exploratory factor analysis to assess structural validity; correlations and group comparisons for construct validity; and Cronbach α for internal consistency. Given the small sample size expected and the likely skewed distribution, it is anticipated that nonparametric statistics will be used (eg, Spearman ρ correlations and unweighted least squares estimation) [20,57].

**Table 2 table2:** Planned psychometric analyses for the ISBUS^a^.

Stage and measurement property		Analysis	Evaluative criteria
Stage 3: final item selection			
	Structural validity		
		If n≥50 but <100: exploratory factor analysis using unweighted least squares for small samples	Loadings ≥0.40 Communalities ≥0.30 Chi-square test *P*>.5 RMSEA^b^<0.08 TLI^c^≥0.90 RMSR^d^≤0.08
		If n≥100: CFA^e^ or EFA^f^; Rasch modelling	CFA: same criteria as EFA Rasch: fit residuals between −2.5 and 2.5 Ordered thresholds
	Hypothesis testing for construct validity		
		Correlate ISBUS burden score with iMCD^g^ quality of life VAS^h^, PHQ-15^i^ score, and EQ-5D-5L utility	At least moderate correlations (rs≥0.30)
		Compare participants with symptoms impacting daily activities vs those without such impact	At least a moderate difference (d≥.05)
	Internal consistency		
		Cronbach α	Cronbach α≥0.70
Stage 4: preliminary measures of change			
	Test-retest reliability		
		ICC^j^ in participants reporting no change in health status	ICC≥0.70
	Measurement error		
		Standard error of measurement and MDC95^k^ in participants reporting no change in health status	MDC95<MIC^l^
	Responsiveness		
		SRM^m^ for improved, stable, and worsened group	SRM≥0.2 (improved and worsened group) and <0.2 (stable group)
		ROC AUC^n^ for improved subgroup	ROC AUC≥0.70 (improved group)
	Meaningful change (MIC)		
		Anchor-based MIC (mean and median improvement) for the minimally improved group	Correlation between anchor and change ≥0.30
		Distributional analyses (0.5 × SD, standard error of measurement) in the improved health group	MIC>MDC95
		Responder difference (mean and/or binary method)	More responders in the improved group than in the nonimproved group
		Triangulate quantitative and qualitative data and expert opinion to refine the MCID^o^ estimate	Used to inform the final MCID recommendation (no threshold applied)

^a^ISBUS: Idiopathic Multicentric Castleman Disease Symptom Burden Scale.

^b^RMSEA: root-mean-square error of approximation.

^c^TLI: Tucker-Lewis index.

^d^RMSR: root-mean-square residual.

^e^CFA: confirmatory factor analysis.

^f^EFA: exploratory factor analysis.

^g^iMCD: idiopathic multicentric Castleman disease.

^h^VAS: visual analog scale.

^i^PHQ-15: Patient Health Questionnaire-15.

^j^ICC: Intraclass correlation coefficient.

^k^MDC95: minimum detectable change at the 95% confidence level.

^l^MIC: minimum important change.

^m^SRM: standardized response mean.

^n^ROC AUC: receiver operating characteristic area under the curve.

^o^MCID: minimal clinically important difference.

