The ISBUS study [22] is an international multistakeholder project conceived through collaboration among industry, clinicians, and patient representatives to design an outcome measure to meet the unmet need to quantify symptom burden in iMCD. The primary aim of this project is to develop and preliminarily evaluate the measurement properties of a novel PROM for capturing symptom burden in people living with iMCD. Symptom burden is typically conceptualized as a multidimensional concept encompassing both the prevalence of multiple symptoms (via their frequency and/or severity) and the perceived impact of these symptoms on the individual experiencing them [23]. This concept has been applied in multiple disease areas. For example, the Memorial Symptom Assessment Scale–Heart Failure asks patients about the frequency, severity, and distress associated with 32 possible symptoms linked to heart failure [24]. Symptom burden is calculated by taking the mean of the 3 responses. Similarly, in cancer, the Patient-Reported Outcomes–Common Terminology Criteria for Adverse Events features items with 1 to 3 ratings of frequency, severity, and/or interference with daily activities, which can be combined into a composite burden score for symptoms experienced during clinical trials [25,26].

In our previous research on iMCD, we identified 26 unique symptoms from a patient survey that impacted at least 11 domains of patients’ daily lives, including physical, mental, and social aspects [8]. These findings informed a condition-specific conceptual model of iMCD symptom burden that guides the design and development of ISBUS (Figure 1). Separately, at a higher level, symptom burden can be conceptualized as a determinant of patients’ HRQoL via its relationship with core domains, such as physical, psychological, and social functioning, recognized as integral to common HRQoL models [27]. Figure 2 presents a more generic conceptual model of the perceived relationship between symptom burden and HRQoL adopted for this study, which helps situate the construct within a wider quality-of-life framework.

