## Results

The ISBUS project was funded in June 2023 and is ongoing at the time of submission. Stage 1 (item generation) began at the start of the project and concluded in December 2023. Stage 2 (item testing and refinement) started in January 2024; interviews with people living with iMCD (n=10) were conducted between May 2024 and September 2024, and this stage concluded in November 2024. Stage 3 began in December 2024. The first survey participant was enrolled in February 2025, and recruitment continued until November 2025, with 51 people living with iMCD completing the survey. Stage 3 concluded in January 2026, when the symptom burden scale was finalized. However, recruitment in Brazil (which is being used for comparative purposes only) is ongoing. Stage 4 is ongoing. As of March 2026, when the paper was submitted, 32 people had completed a follow-up survey, and the qualitative interviews on meaningful change were ongoing. A scale development paper (featuring the results from stages 1-3) is expected to be published in 2026, with a further paper on understanding change (stage 4) published in 2027. In accordance with established best practice [17], a user manual will be produced for the new PROM describing, among other aspects, how to score and administer the measure.

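### Unweighted least squares does not deal with the expected skew: unless adjusted for non-normality, the RMSEA, TLI and chi-square criteria in Table 2 will often fail a sound one-factor scale at n=51

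*Protocol article*

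**What the plan says.** In the Stage 3 Analysis section the reason comes first: "Given the small sample size expected and the likely skewed distribution". The response follows in the same sentence: "it is anticipated that nonparametric statistics will be used (eg, Spearman ρ correlations and unweighted least squares estimation".

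For samples of 50 to 99, the structural validity row of Table 2 prescribes "exploratory factor analysis using unweighted least squares for small samples". Its criteria include "Chi-square test *P*>.5" and "RMSEA^b^<0.08 TLI^c^≥0.90 RMSR^d^≤0.08", next to loadings of at least 0.40 and communalities of at least 0.30.

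Under Stage 3 recruitment, "an absolute minimum target sample size of 50 is adopted". The Results section reports that Stage 3 closed "with 51 people living with iMCD completing the survey", so this row is the one that applies.

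The article does not state the correlation matrix to be factored, whether the fit indices are scaled for non-normality, the number of items, or how strong the skew is. It gives no rule that ties the number of factors to RMSEA or TLI. The final content is to be agreed with advisors from all the evidence.

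**The concern.** The sentence identifies a problem (skew), names a remedy (ULS), and the remedy does not reach three criteria in the row that uses it. ULS gives every residual correlation equal weight when loadings are fitted. That step needs no normality, so the loading and communality criteria are not at issue here. RMSEA and TLI, however, are functions of a chi-square whose usual reference distribution assumes multivariate normal items, and so is the chi-square P. With skewed items that statistic is inflated even when the model is right.

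Stage 3 is meant to inform item selection and supply the first structural validity evidence, and the project relies on one overall burden score. A sound single scale could be reported as structurally poor only because many respondents lack many symptoms. This problem is separate from the choice of cut-offs: changing a cut-off leaves the reference distribution wrong.

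**Working it through.** **No figure to reproduce.** The article derives nothing numerical from these criteria, so the check is a simulation in which one factor is the truth.

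**Inputs from the article.** n=51; ULS; RMSEA<0.08; TLI≥0.90. The Introduction mentions that "we identified 26 unique symptoms from a patient survey", which motivates 26 as an upper item count.

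**Assumed inputs.** 10 to 26 items; loadings 0.6 and 0.75; five response levels. Moderate skew means 55/20/12/8/5% across the levels (skewness 1.2). Heavy skew means 75/12/7/4/2% (skewness 2.2). A mixed setting varies skew across items.

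**Formulas**, for p items and one factor:
- df = ((p−1)² − (p+1))/2 and df₀ = p(p−1)/2
- X² = m × F, where F is the normal-theory discrepancy at the ULS solution. Uncorrected m = n−1; Bartlett m = n−1−(2p+5)/6−2/3. The null-model X₀² omits the 2/3.
- RMSEA = √(max[(X²−df)/(df(n−1)), 0])
- TLI = (X₀²/df₀ − X²/df)/(X₀²/df₀ − 1)

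**Step 1: what RMSEA<0.08 demands.** It requires X² < df × (1 + 0.08² × 50) = 1.32 × df. With 10 items, df = (81−11)/2 = 35, so X² must stay below 46.2.

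**Step 2: what skew does to X².** The estimated scaling factor (roughly the average of X²/df for a correct model) was, over 10 and 15 items:
- normal items: 0.96
- moderate skew: 1.20 to 1.40
- heavy skew: 1.52 to 1.91

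Moderate skew therefore puts a correct model close to the 1.32 limit on average, and heavy skew puts it beyond.

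**Step 3: share of true one-factor samples passing both RMSEA and TLI**, Pearson matrix, n=51, shown as uncorrected / Bartlett-corrected:

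| Items, loading | Normal | Moderate skew | Heavy skew | Mixed skew |
|---|---|---|---|---|
| 10, 0.6 | 76% / 87% | 28% / 40% | 7% / 11% | 50% / 65% |
| 15, 0.75 | 84% / 98% | 7% / 18% | 0% / 0% | 29% / 61% |
| 26, 0.6 | 8% / 88% | 0% / 2% | not shown | 0% / 21% |

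Symmetric five-level items (10 items, loading 0.6) pass in 74% / 85%, almost as often as normal items. The loss comes from skew, not from having five categories. A separate simulation over 10-20 items, Bartlett-corrected, gave 87-99% with normal items, 8-40% with moderate skew and 0-13% with heavy skew.

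**Step 4: does a rank matrix rescue it?** Only partly. With a Spearman matrix over 10-20 items, 27-61% pass under moderate skew and 0-27% under heavy skew.

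**Step 5: does scaling rescue it?** Partly. With a mean-scaled (Satorra-Bentler type) statistic, 10 and 15 items, moderate-skew passes rise from 16-44% to 57-75%. Under heavy skew only 27-53% pass.

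**Step 6: if factors were added until both indices pass** (10 and 15 items, Bartlett-corrected), two or more would be needed in 56-84% of moderate-skew samples and 91-100% of heavy-skew samples, against 3-16% with normal items. Parallel analysis on column-permuted data kept exactly one factor in 93-100% of comparable one-factor samples.

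**The case against.** The strongest reply is that the article does not say how RMSEA and TLI are computed. Matrix and scaling are details an article may leave to the full plan, and Spearman correlations are named in the same sentence. This stands in part: a reader might infer that the indices are certainly unadjusted, and the text does not support that. But the point does not rest on the omission. The article states a remedy for skew, and that remedy does not do the job. A Spearman matrix does not close the gap either.

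A reader might also infer that the plan adds factors until the indices pass, so that subscales will reflect skew. Nothing in the article says so: Table 2 lists evaluative criteria, not a retention rule, and advisors weigh all the evidence. Step 6 is therefore conditional. The risk of misreporting structural validity does not depend on it.

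The rates rest on assumed items, loadings and skew. With mixed skew and Bartlett correction, 61-65% still pass in the 10- and 15-item rows of the table. Skew is also not the only cause: with 26 normal items at loading 0.6, uncorrected indices pass only 8%, because n is small relative to the item count. For that reason the headline comparison uses Bartlett-corrected values, where normal items do well and the remaining loss is due to skew.

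Finally, Table 2 justifies ULS by small samples, which is a fair reason to use it. Only the claim that it is a nonparametric answer to skew fails.

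**Conclusion.** The point holds as a conditional one. ULS is wrongly presented as a nonparametric response to skew. Unless RMSEA, TLI and chi-square are adjusted for non-normality, the Table 2 criteria cannot be read at face value for skewed items at n=51. The Bartlett-corrected pass rate for a correct one-factor scale of 10-20 items falls from 87-99% to about 8-40% under moderate skew and 0-13% under heavy skew. The exact loss depends on item count, loadings and skew, none of which the article gives. It shrinks when only some items are skewed and grows with more items. Retention of too many factors is a possible further consequence, only if the indices are also used to choose the number of factors.

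**What to change.** 1. In the Stage 3 Analysis section, keep ULS as the small-sample estimator but remove it as an example of a nonparametric statistic and as the answer to skew.
2. State the correlation matrix used. Treat RMSEA, TLI and the chi-square P as criteria only when they come from a mean-and-variance-adjusted or bootstrap statistic; otherwise report them descriptively at n=51.
3. Support the number of factors with parallel analysis on column-permuted data, which keeps each item's own skew, using the Spearman or polychoric matrix.

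**Cost.** A wording change and a short re-analysis of data in hand. The scale was finalized in January 2026, but the paper on stages 1-3 is still expected in 2026, so the results can be reported this way. A different factor count would, however, raise questions about decisions already taken.

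**Limits.** Scaling helps only partly under heavy skew (27-53% pass with the mean-scaled statistic tested), which favours descriptive use. Permutation parallel analysis can keep too few factors at this size: with skewed items and three factors correlated 0.5 it kept all three in about 32% of samples, against 84% at correlation 0.3. It should be read together with the loadings and advisory input.

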**Objective:**

This protocol describes the international multistakeholder Idiopathic Multicentric Castleman Disease Symptom Burden Scale (ISBUS) project. The primary aim of this project is to develop and preliminarily evaluate the measurement properties of a novel PROM for capturing symptom burden (ie, perceived symptom frequency and impact on daily life) in people living with iMCD. The central objective is to produce a valid and robust PROM that can be used to assess iMCD symptom burden in research, clinical trials, and symptom monitoring in clinical practice.

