Smaller samples are inevitable in rare disease research, and this limits what can be done in terms of psychometric analysis. The multinational approach of the ISBUS project helps to address this, but implicit in this approach is the assumption that the survey operates equivalently across different primarily English-speaking countries (due to the expected small sample sizes from different countries, it may be impractical to test this assumption formally). While samples could be expanded by recruiting patients with sufficiently analogous conditions [20], this decision risks undermining the goal of the novel PROM and its unique applicability to people living with iMCD. Instead, methods will be adapted for smaller samples, with any limitations transparently noted during dissemination [30]. In addition to the smaller sample size being challenging, the fact that iMCD is an episodic condition in which symptom burden is related to the activity of the disease and the treatment that the patient is receiving means that the timing of survey administration is important. We aim to address this by enrolling as many patients as possible in the hope that patients experiencing initial flares, relapses, and remissions will all be captured.

Another limitation to consider is the reliance on self-reported diagnosis. However, methods including a robust, clinically informed screener and dual recruitment routes (ie, via the CDCN and clinically verified patients with iMCD) help to offset this. Further, the reliance on online data collection is a pragmatic and advisable choice in rare disease research [19], but may limit inclusion of those who choose not to, or are unable to, take part in online studies. Reassuringly, research suggests switching from online to paper-based administration (or vice versa) is likely to have only a minor influence on responses [52]. Finally, the estimates of change in stage 4 should be considered preliminary only, as they are derived from a natural history approach (ie, noninterventional). While our approach is strengthened by triangulation of multiple methods, estimates such as the standardized response mean (responsiveness) may form a lower bound of sensitivity to change (as no direct study intervention was administered) and should be considered conservative.

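### The known-groups test appears to pool symptom-free respondents with symptomatic respondents without impact, so it says little about impact, and its printed cutoff (d≥.05) is not moderate

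*Protocol article*

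**What the plan says.** The Stage 3 Data Collection section describes a single background question on how iMCD symptoms affect daily activities, "split into 3 options: no symptoms, symptoms but no impact on daily activities, and symptoms that are impacting daily activities". It is asked before the draft ISBUS and is not one of its items.

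Table 2 (Stage 3 Analysis, hypothesis testing for construct validity) turns this into a two-group contrast: "Compare participants with symptoms impacting daily activities vs those without such impact". The evaluative criterion is "At least a moderate difference (d≥.05"). Table 2 lists no three-level comparison and no contrast restricted to symptomatic respondents.

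The Abstract defines the construct as "perceived symptom frequency and impact on daily life". The Results section reports the stage 3 sample, "with 51 people living with iMCD completing the survey", against a planned floor: "an absolute minimum target sample size of 50 is adopted". Under Strengths and Limitations, the authors hope that "patients experiencing initial flares, relapses, and remissions will all be captured", so some symptom-free respondents are plausible. Their number is not reported.

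**The concern.** On a plain reading, respondents without such impact are all those who did not choose the third answer. That group then mixes two kinds of people: those with symptoms that do not affect daily activities, and those with no symptoms at all.

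The second kind should score low on any symptom list, including one that ignores impact. If enough of them are in the group, the standardized difference can pass the criterion mainly because of them.

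This matters because the Introduction faults the existing MCD symptom scale for not explicitly capturing perceived impact on daily life. Impact is thus part of what ISBUS claims to add. The known-groups row is the only listed test that groups patients by impact on daily activities. A pass on the pooled contrast could be reported as evidence that ISBUS discriminates impact when the contrast that bears on that claim has not been examined.

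The criterion adds a second problem: a d of .05 is close to no difference, yet the row calls it moderate.

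**Working it through.** The article gives no power or sample-size calculation for this contrast, so there is no figure of its own to reproduce.

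**Inputs from the article:** N=51; a three-level item; a two-group contrast; cutoff d≥.05, labelled moderate.

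**Assumptions not in the article:** 31 respondents with impact and 20 in the comparison group, k of whom are symptom-free. Symptomatic respondents without impact have mean 0 and SD 1; those with impact have mean 0.2 and SD 1. Symptom-free respondents have mean −g and SD 0.2, with g from 1 to 2. The intended moderate cutoff is taken as 0.5.

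**Step 1: the cutoff alone, no pooling, no true difference.**
- SE of d ≈ √(1/31 + 1/20) = √0.0823 = 0.287.
- P(d≥.05) = 1 − Φ(0.05/0.287) = 1 − Φ(0.174) ≈ 43%.
- P(d≥0.5) = 1 − Φ(0.5/0.287) = 1 − Φ(1.743) ≈ 4%.

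Other splits of 51 (25/26, 35/16, 40/11) give 43-44% and 4-7%. The printed cutoff therefore barely screens anything, whoever is in the comparison group.

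**Step 2: expected d when k of the 20 are symptom-free.** With w = k/20:
- comparison mean = −w·g
- comparison variance v = (1−w) + 0.04w + w(1−w)g²
- pooled SD = √[(30 + 19v)/49]
- expected d ≈ (0.2 + w·g)/pooled SD

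| k | g | v | pooled SD | expected d |
|---|---|---|---|---|
| 0 | – | 1.000 | 1.000 | 0.20 |
| 4 | 1 | 0.968 | 0.994 | 0.40 |
| 4 | 2 | 1.448 | 1.083 | 0.55 |
| 8 | 1 | 0.856 | 0.972 | 0.62 |
| 8 | 2 | 1.576 | 1.106 | 0.90 |

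**Step 3: chance of meeting d≥0.5, by simulation under the same assumptions.**

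| Symptom-free, of 20 | Pooled contrast, g from 1 to 2 | Symptomatic-only contrast |
|---|---|---|
| 0 | about 16% | about 16% |
| 4 | 36-58% | about 17% |
| 6 | 51-81% | about 18% |
| 8 | 67-95% | about 19% |

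At the printed cutoff of .05, the pooled contrast with four symptom-free respondents passes 90-98% of the time.

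**Step 4: a stricter case, no true difference among symptomatic respondents.** Take a 30/21 split, symptom-free respondents exactly at the scale minimum, and symptomatic respondents 1 to 2 SD above it. The expected pooled d reaches .05 once about 2.5-5% of the comparison group is symptom-free. It reaches 0.5 only at about 28-48%.

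**The case against.** Several points on the other side are sound.

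- **Pooling is inferred.** Table 2 does not say that the two non-impact answers are merged, and the phrase could mean only symptomatic respondents without impact. A condensed article may leave this definition to the full protocol. That stands as a caution. Even so, the row as printed reads most naturally as pooling, and it is the stated analysis.
- **A reader might infer that symptom-free respondents sit at the ISBUS minimum by construction.** The article does not support this. It gives no scoring rule or score range, and someone who answers that they have no symptoms could still endorse items on a long list. Low scores are an expectation.
- **A reader might also infer that a pass would show no real discrimination.** That goes too far. The construct includes symptom frequency as well as impact, so separating symptom-free from impacted patients is real discrimination, if an easy test. What a pooled pass leaves open is discrimination of impact among symptomatic patients.
- **The size depends on unknowns.** If the true symptomatic difference were 0.8, the contrast would reach 0.5 about 85% of the time with no symptom-free respondents (1 − Φ((0.5 − 0.8)/0.287) = Φ(1.05)), and pooling would seldom change the conclusion. With few symptom-free respondents the effect is modest.
- **The test does not stand alone.** Table 2 also plans correlations with the quality-of-life VAS, PHQ-15 and EQ-5D-5L. None of these compares patients grouped by impact on daily activities, so they do not replace the missing contrast.

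**Conclusion.** The point holds in a limited form. A three-level item is reduced to a two-group contrast whose comparison group, read plainly, includes symptom-free respondents. Those respondents can carry the criterion when ISBUS separates impact from no impact only weakly among symptomatic patients. With a true symptomatic d of 0.2 and 51 respondents, four to eight symptom-free respondents raise the chance of d≥0.5 from about 16% to somewhere between 36% and 95%, depending on their number and how low they score. This rests on the assumed split, the assumed gap and an unknown symptom-free share. It shows what the test could conceal and does not show that ISBUS discriminates poorly.

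The contradiction in the cutoff does not depend on those assumptions: moderate and d≥.05 cannot both be meant, and 0.5 was presumably intended. Removing symptom-free respondents would not repair it, because a null contrast would still meet .05 about 43% of the time.

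**What to change.** 1. State in Table 2 which answers form the comparison group.
2. Report ISBUS scores for all three answer levels, with the number in each, and add an ordered trend test such as Jonckheere-Terpstra.
3. Report symptomatic respondents with impact against symptomatic respondents without impact, giving d and its confidence interval. Base any claim that ISBUS discriminates impact on this contrast.
4. Correct the cutoff so that the number and the word moderate agree (presumably 0.5).

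**Cost.** The data are already collected. The Results section says that the scale was finalized in January 2026 and that the stages 1-3 paper is still to come, so this is a short supplementary re-analysis.

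The contrast becomes smaller and less precise, and the observed d will probably fall. With 31 vs 16 and d=0.5, the 95% half-width is about 1.96 × √(1/31 + 1/16 + 0.25/94) = 0.61, against 0.57 for 31 vs 20 (last term 0.25/102). A scale with a true d of exactly 0.5 would reach an observed 0.5 only about half the time, so the interval should be read alongside the pass or fail result.
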